## Abstract

**Background:**

During the COVID-19 pandemic, many people have experienced traumatic losses and therefore are at risk of developing complicated grief regarding the restrictions on the performance of routine mourning rituals. This study is a randomized controlled trial for assessing the efficacy of three versus five sessions of grief counseling on grief intensity, psychological distress, and quality of life of grief among bereaved people due to COVID-19.

**Methods:**

A total of 120 bereaved people, due to COVID-19, will be enrolled in this multi-center randomized controlled trial after assessment for inclusion and exclusion criteria. Following the informed consent procedure, participants will be allocated into two groups equally by the Stratified Balanced Block Randomization, one of them delivering a three-session grief counseling intervention and the other delivering a five-session grief counseling intervention. The intervention will be delivered by trained psychologists *via* in-person individual sessions. The primary outcome is grief intensity, and the secondary outcomes are psychological distress, quality of life, and satisfaction of the participants. These outcomes will be measured by the Grief Intensity Scale (GIS), the General Health Questionnaire-28 (GHQ-28), the Short Form Health Survey-12 (SF-12), and the Client Satisfaction Questionnaire (CSQ-8), respectively. The assessments will be done at three time points, one before the intervention and the others 1 month and 3 months after the intervention. The data will be analyzed using the SPSS V.18 and Stata V.11 software. The analysis approach will be “intention to treat.”

**Discussion:**

Results of this study can be applied for selecting the most suitable intervention leading to the prevention of complicated grief and the maintenance and promotion of the mental health of bereaved people due to COVID-19.

**Clinical trial registration:**

[irct.ir], identifier [IRCT20200505047305N1].

## Introduction

Grief is an emotional reaction manifesting as deep sadness and regret and a range of other feelings which an individual experiences following the loss of a loved one (1). The concept of grief is mainly related to the various reactions and mental feelings that individuals experience after a loss and especially death of an intimate person (2, 3). Grieving individuals may not ever return to their previous emotional status but are usually able to go on with their lives and let go of their pain and eventually start to build new relationships (4, 5). This process happens in a process named bereavement. Bereavement is a universal reaction to loss, and individuals come to an acceptance of it over a period of about 6 months to 1 year; their attachment to the lost one loosens as they come back to normal life (6, 7). Although grief is a normal reaction, it is accompanied by various feelings. Some are able to handle the loss and cope with it through the mourning process, and others experience severe sorrow throughout a long period. These severe emotional reactions are poor prognostic factors and predictors of a prolonged grief disorder or complicated grief (8). Based on International Classification of Diseases 11th Revision (ICD-11), prolonged grief disorder is a disturbance in which, following the death of a person close to the bereaved, there is persistent and pervasive grief response (more than 6 months at a minimum) and causes significant impairment in personal, family, social, educational, occupational, or other important areas of functioning (9). The DSM-5 (diagnostic and statistical manual of mental disorders, fifth edition) proposed “persistent complex bereavement disorder” as a psychiatric disorder categorized under the entity of stress-related disorders (1). Individuals diagnosed with persistent complex bereavement disorder are also at an increased risk of mental health and other health problems. This may also affect their behavior and at times lead to suicidal ideation or attempts, necessitating therapeutic interventions (10). We know that COVID-19 has many physical and mental consequences, including lung, kidney and liver complications, drug-related complications, depression, anxiety, and psychological distress (11–14). The high prevalence of psychological distress, stress reaction, insomnia symptoms, and the increased burden of mental disorders during the pandemic provide evidence for the serious impact of COVID-19 on mental health (15, 16).

Ever since the COVID-19 outbreak began, many people have been experiencing loss and are going through tragic processes of shock and denial (17, 18). Evidence shows that following sudden and unpredictable deaths such as deaths due to COVID-19, grief levels are higher, and grief reactions are more intense and, therefore, may convert to complex or prolonged grief disorder (8, 19–22). In this case, Tang and Xiang reported a high prevalence of prolonged grief disorder among people bereaved due to COVID-19 (23). These bereaved people have to face fears of virus transmission during corpse handling, which leads to limitations in the burial process alongside their deep anguish, and they have no opportunities to say goodbye (21, 24). Social distancing measures simultaneously hinder the performance of routine mourning rituals and ceremonies, which otherwise would have a facilitating role in the grieving process for the individual. Mourning is a societal process, and bereaving individuals are in need of social support to be able to go through it; nevertheless, in COVID-19 cases, social support is mainly absent (24–26).

Grief counseling is a psychological intervention that assists bereaving individuals manage their emotions throughout the grief process (8). Evidence-based interventions for reducing the burden of suffering on bereaved individuals have been proven to decrease long-term health risks and are beneficial in improving clinically relevant outcomes (27). Psychological interventions in grieving individuals have both immediate and long-term effects on grief, especially when delivered individually (28). Greater symptom change has been observed in people at risk for developing persistent complex bereavement disorder in the long term and after the intervention has been completed, and this shows that counseling helps more than the passage of time alone (29). For individuals diagnosed with persistent complex bereavement disorder, psychological interventions are quite different and are consisted of specific techniques (8).

The study aims at comparing the efficacy of providing three versus five sessions of a grief counseling intervention to family members of those deceased due to COVID-19 in the setting of a multi-center randomized clinical trial. The primary outcome measure is the intensity of grief of individuals after a 3-month follow-up period. Quality of life, psychological distress, and satisfaction with the intervention are the secondary outcomes that will be compared among both groups. In this study, in addition to a general investigation of the efficacy of grief counseling, we aimed to compare the efficacy of three- and five-session grief counseling. If similar efficacy is seen between the two groups due to a lack of resources, three-session counseling can be introduced to the authorities as a population-based intervention for bereaved people in the country. In this case, by spending less time and money, more bereaved people will benefit from this service.

We hypothesize that the effect of the three-session grief counseling intervention on the grief intensity, psychological distress, quality of life, and satisfaction with the intervention among participants will be comparable with the five-session intervention and supposedly have equal efficacy.

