## Methods

### Study design

This study is a parallel multi-center randomized controlled trial for comparing the efficacy of a three- versus five-session counseling intervention on bereaved people who had lost a loved one due to COVID-19 by dividing them into two equal intervention groups.

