### Recruitment process

Five of the researchers will be in direct connection with the 10 medical universities. In every university, two health centers will be selected for service delivery, and one trained clinical psychologist will be the service provider in each center. The clinical psychologist obtains names and phone numbers of bereaved people on a routine basis from the social service department of the hospitals in the catchment area of the center and will invite them by phone to encourage them to attend the grief counseling sessions. The clinical psychologist will also try to create effective communication and express compassion and empathy toward the grieving individuals. When participants attend health centers, their demographic data are obtained and registered, and the inclusion or exclusion criteria will then be re-assessed. If inclusion criteria exist and in the absence of the exclusion criteria, the participant will be thoroughly informed on the designed counseling intervention process, and informed consent will be obtained. If several family members of one COVID-19 victim attend the health center to receive service, only one of them will be enrolled in the study, and the rest will be directed to receive the usual grief counseling services provided at health centers. Assessments will be done at three time points, one before the intervention and the others 1 month and 3 months after the intervention.

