### Randomization

After informed consent, participants are randomized into three- or five-session intervention groups. Allocation of participants to each group will be done with the use of Stratified Balanced Block Randomization. Twelve participants will be selected from each university, and randomization will be done separately for each. Among 20 possibilities for six blocks including forms of three individuals in the five-session group and three individuals in the three-session group, two blocks will be randomly chosen for each university in the Microsoft Office Excel software with the use of the RANDBETWEEN formula and a random sequence will be formed. Subsequently, participants will be divided into the three- and five-session groups equally according to the random sequence. Randomization will be done in the main research headquarters in the Mental Health Research Center of the IUMS, and information will be only given to the health centers at the time of initiation of the intervention.

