### Planned analysis

The data, after entering and cleaning, will be analyzed using the SPSS V.18 and Stata V.11 software. Mean and standard deviation will be calculated to continuous data and frequency, and percent will be used for showing categorical variables. The analysis approach will be “intention to treat.” An independent and paired *t*-test, a chi-square, and a repeated-measures ANOVA (non-parametric tests if necessary) will be used to compare the studied outcomes in the follow-ups between and within the groups. The generalized estimating equations (GEEs) will be fitted in separate models for each outcome, and α < 0.05 will be considered as statistical significance.

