## Discussion

This study is a multi-center randomized controlled trial for comparing the efficacy of a three-session versus a five-session counseling intervention on the bereaved people of those deceased due to COVID-19 regarding the intensity of grief, psychological distress, quality of life, and satisfaction with the services. In the recent COVID-19 outbreak, many people lost their loved ones without being able to perform mourning ceremonies due to safety protocols and were deprived of the necessary social support they could have received otherwise from their family members and friends, putting them at risk of later developing complicated and prolonged grief disorder as health crisis due to COVID-19 (21, 23, 38). This study is a multi-center randomized controlled trial with the objective of preventing psychological problems in bereaved people due to COVID-19, being conducted for the first time in Iran. In addition to a general investigation of the efficacy of grief counseling, we aimed to compare the efficacy of three- and five-session grief counseling. If similar efficacy is seen between the two interventions, the three-session counseling can be introduced to the authorities as a population-based intervention for bereaved people in the country. In this case, by spending less time and money, more bereaved people will benefit from this service.

The results of this study will facilitate policymakers, planners, clinicians, and other service providers to design proper interventions for the prevention of complicated and unexpressed grief among the bereaved people due to COVID-19, and this can have a vast effect on the mental health of the society in the COVID-19 and post-COVID-19 era.

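### The stated aim of assessing grief counselling in general cannot be met: both arms are counselled, and within-group change cannot be separated from natural easing of grief

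*Protocol article*

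**What the plan says.** The Introduction sets out two aims in one sentence: "in addition to a general investigation of the efficacy of grief counseling, we aimed to compare the efficacy of three- and five-session grief counseling". The Discussion restates both: "In addition to a general investigation of the efficacy of grief counseling, we aimed to compare the efficacy of three- and five-session grief counseling". The general aim is thus written as something beyond the head-to-head comparison.

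The design has two active arms. Study design compares three with five sessions "by dividing them into two equal intervention groups", and Randomization confirms that "After informed consent, participants are randomized into three- or five-session intervention groups". Other relatives of the same deceased person are not enrolled. Recruitment process says that "the rest will be directed to receive the usual grief counseling services provided at health centers", and no outcome assessment of them is described.

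Planned analysis lists independent and paired t-tests, chi-square tests and repeated-measures ANOVA, which "will be used to compare the studied outcomes in the follow-ups between and within the groups", and adds GEE models for each outcome.

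On the natural course of bereavement, the Introduction says that "individuals come to an acceptance of it over a period of about 6 months to 1 year".

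**The concern.** An aim to establish whether counselling works needs a group without it, or some other estimate of what would have happened anyway. This trial has neither. What remains is the before-after change among people who were all counselled. That change mixes any effect of counselling with the ordinary course of grief after a recent death, and with regression to the mean.

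At stake is the interpretation of a significant fall in the Grief Intensity Scale. A reader who takes the general aim at face value would naturally read such a fall as the answer to it. The same gap limits a finding of similarity. Two packages that both work, and two that both do nothing, can give the same between-arm result.

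**Working it through.** **1. Which analysis could serve the general aim?**

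- The between-arm tests (independent t-test, group terms in the ANOVA or GEE) contrast three with five sessions. They carry no information on counselling versus none.
- The within-arm tests (paired t-test, time effect in the repeated-measures ANOVA, any time term in the GEE) measure change from baseline. They are the only candidates, and none has an uncounselled reference.

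**2. What period does the change cover?**

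- Counselling starts 2 weeks after the death (Inclusion and exclusion criteria), and baseline comes just before it.
- Five weekly sessions: 4 intervals × 1 week = 4 weeks. Three fortnightly sessions: 2 intervals × 2 weeks = 4 weeks.
- The last assessment is 3 months, about 13 weeks, after counselling ends (Recruitment process).
- 2 + 4 + 13 = 19 weeks after the death, about 4.4 months.

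The whole observation period lies inside the course that the Introduction describes, and ends before its 6-month lower mark. Some easing is therefore to be expected, but the documents do not say how much.

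**3. The plan's own figure.** The protocol gives no figure for the general aim. Its only size calculation is 60 per group for the between-arm comparison (d = 0.5, α = 0.05, power 80%, drop-out 20%). By the normal approximation with a one-sided α, n = 2(1.645 + 0.842)² / 0.5² = 49.5, so 50, and 50 × 1.2 = 60. A two-sided α gives 63 before drop-out and does not lead to 60. That is a separate matter. All that is needed here is the number of completers: 60 × 0.8 = 48 per arm, or 96 in total.

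**4. Illustration: how often would a paired test be significant if counselling did nothing?** Let dz be the mean natural change divided by the SD of the change score. The paired t statistic then follows a noncentral t distribution with n − 1 degrees of freedom and noncentrality dz × √n. The dz values are assumptions.

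| dz (assumed) | n = 48: dz × √48 | Chance of p < 0.05, one arm | n = 96: dz × √96 | Chance of p < 0.05, arms pooled |
|---|---|---|---|---|
| 0.2 | 1.39 | 27% | 1.96 | 49% |
| 0.3 | 2.08 | 53% | 2.94 | 83% |
| 0.5 | 3.46 | 92% | 4.90 | 99.8% |

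If all 60 per arm were analysed, the one-arm figures would be 33%, 63% and 97%.

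If natural change is instead stated as D in SDs of the score, then dz = D / √(2(1 − r)), where r is the correlation between baseline and follow-up. For D = 0.3 and r = 0.3, 0.5 and 0.7, dz is 0.25, 0.30 and 0.39, and the one-arm chance with 48 completers is 41%, 53% and 75%.

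**5. Is the randomized comparison affected?** A simulation used 20,000 trials with 48 per arm, r = 0.5, no counselling effect and the same natural change in both arms. The between-arm test was significant in 5.0% of trials at D = 0.3 and 5.2% at D = 0.5, in line with its nominal 5%. Natural easing is common to both arms and cancels in that contrast.

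**The case against.** The general aim is a subordinate clause. It has no hypothesis, outcome or sample size of its own. The abstract, the formal hypothesis, the design and the size calculation all concern three versus five sessions. This stands, and it confines the problem to one stated aim. It does not remove that aim, which appears twice.

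The protocol never says that paired tests will be its evidence of efficacy. This also stands: the link is an inference from the lack of any other analysis that could serve. A reader might go further and infer that the trial will almost surely declare counselling effective and recommend it nationally. The documents do not support that. The recommendation in the Introduction and Discussion depends on similar efficacy between the arms, not on a significant paired test, and at dz = 0.2 a single-arm test would be significant only 27% of the time.

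A reader might also call the percentages above a false-positive rate in place of 5%. They are not. The paired test has correct size for its own null of no change, and rejecting that null when grief has truly eased is power. The error would lie in attributing the change to counselling.

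The natural course should not be overstated either. The Introduction speaks of acceptance, not resolution. It adds that some people suffer severely for a long time and that grief after COVID-19 deaths may be more intense.

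Finally, a comparison of two active versions may lean on earlier evidence, and the Introduction cites outside work that counselling does better than time alone. That is a legitimate premise. But it is cited for people at risk of persistent complex bereavement disorder, and this trial does not select on that risk. Whether it carries over cannot be judged from the documents, and this design does not test it.

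**Conclusion.** The concern holds for the general-efficacy aim alone. With both arms counselled and no other group assessed, the trial cannot say whether grief counselling works, and no later analysis plan can supply the missing comparator. Within-arm change from about week 2 to about week 19 is a mixture that cannot be separated.

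This conclusion rests on the design, not on the arithmetic. The 27%, 53% and 92% are illustrative. They assume no counselling effect, natural change of 0.2, 0.3 or 0.5 SD of the change score, 48 completers per arm and a two-sided 5% paired t-test. The documents give neither an SD nor a natural-change figure.

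A reader might infer that natural easing also biases the three- versus five-session comparison. It does not, because randomization balances it. The limit is on interpretation: similar arms would not by themselves show that either is better than no counselling or than usual services. That step rests on the outside evidence the Introduction cites.

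**What to change.** - **Introduction and Discussion:** delete the general-efficacy aim, or reword it as describing change in grief over time among counselled participants.
- **Planned analysis:** state that within-arm change is descriptive, reported as estimates with confidence intervals, and is not evidence of efficacy.
- **Conclusions:** limit them to the relative effect of three versus five sessions. Say that similarity does not establish superiority to no counselling or to usual services, and that any such claim relies on the cited outside evidence.

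Sample size, assessments, randomization and conduct stay as they are. The cost is giving up an efficacy claim that the design cannot support.

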### Data collection/management process

The primary outcome measure is the grief intensity based on the grief intensity scale (GIS) score of individuals receiving grief counseling sessions after a 3-month follow-up period, and the secondary outcomes are the quality of life, psychological distress, and satisfaction with the services. In this study, one qualified clinical psychologist will be entitled to each medical university attending two of the health centers to collect data at three points of participant entry (baseline assessment) and two follow-up points at 1-month and 3-month follow-up periods. Satisfaction with the services will be assessed at the end of the counseling sessions (either three or five) and 3-month after it. Clinical psychologists who are working as raters will be trained to use the questionnaires, and inter-rater reliability will also be checked after the training sessions. To reduce the risk of research bias, the raters will not be among those clinical psychologists providing the grief counseling sessions and will be blind toward the number of sessions each individual has received.

Demographic variables will be obtained using a questionnaire created by the researcher, and data collection for obtaining the dependent variables of the study will be performed by using the GIS, the General Health Questionnaire (GHQ-28), the Short Form Health Survey (SF-12), and the Client Satisfaction Questionnaire (CSQ-8).

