### Sample size calculation

The sample size has been calculated to be 60 individuals in each group, which is a total of 120 individuals. Twelve individuals will be selected from two health centers of each of the 10 universities. This calculation has been done using the G*Power software (37) for comparing the grief intensity score as the primary outcome among the two groups and based on the results of the pilot study. In this calculation, the type one error (α) is 0.05, the type two error (β) is 0.2, the effect size (d) is 0.5, and the drop-out expectation is 20% of the participants.

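### The trial sets out to show that three sessions are as good as five, but it is sized and tested only for a difference, so a null result could pass as similarity

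*Protocol article*

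**What the plan says.** The Introduction of the protocol article states the hypothesis that the effect of three sessions "will be comparable with the five-session intervention and supposedly have equal efficacy". It attaches a policy step to that result: "If similar efficacy is seen between the two groups due to a lack of resources, three-session counseling can be introduced to the authorities". The Discussion repeats it: "If similar efficacy is seen between the two interventions, the three-session counseling can be introduced to the authorities".

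The Data collection/management process section names the endpoint: "The primary outcome measure is the grief intensity based on the grief intensity scale (GIS) score", taken after 3 months of follow-up. A higher score means more intense grief.

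The Sample size calculation section arrives at 60 per group from four inputs: "the type one error (α) is 0.05", "the type two error (β) is 0.2", "the effect size (d) is 0.5" and 20% drop-out. It gives no sidedness and does not call 0.5 a margin.

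The Planned analysis section lists t-tests, chi-square, repeated-measures ANOVA and GEE on an intention-to-treat basis. Its one criterion is that "α < 0.05 will be considered as statistical significance".

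**The concern.** The hypothesis and the policy decision are about the absence of a material difference. The tests and the effect size belong to a trial looking for a difference. With no definition of similar, p > 0.05 is the only result in the plan that could be offered in support of the hypothesis.

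That reverses the usual incentives. A smaller sample, more drop-out, noisier measurement or poorer session attendance all make a non-significant result more likely, and so make the hypothesis look better supported. The shorter package could be recommended nationally although a material loss of benefit had not been excluded.

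This is not a detail for a later analysis plan. Whether a trial tests difference, non-inferiority or equivalence determines its sample size, and the protocol has already fixed that size.

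**Working it through.** **Inputs.** From the Sample size calculation section: α = 0.05, β = 0.2, d = 0.5, 20% drop-out, 60 per arm. Completers per arm: 60 × 0.8 = 48. The article gives neither the pilot SD nor a margin, so everything below is in SD units and the margins of 0.3, 0.4 and 0.5 SD are assumptions.

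**1. The plan's own figure.** n per arm = 2 × ((z for α + z for power) / d)².
- Two-sided 0.05: 2 × ((1.960 + 0.842)/0.5)² gives 63. Dividing by 0.8 gives 79, and multiplying by 1.2 gives 76. Neither is 60.
- One-sided 0.05: 2 × ((1.645 + 0.842)/0.5)² gives 50. Multiplying by 1.2 gives 60; dividing by 0.8 gives 63.

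So 60 is reproduced exactly by a one-sided 0.05 calculation with × 1.2 inflation. The article states neither.

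**2. Chance of a non-significant result when three sessions really are worse.** Two-sided 0.05 t-test, noncentral t; probability = 1 − power.

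| True deficit | 48 per arm | 60 per arm (no drop-out) |
|---|---|---|
| 0.3 SD | 69% | 63% |
| 0.4 SD | 51% | 42% |
| 0.5 SD | 32% | 22% |

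Every entry rises as participants are lost.

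**3. What a non-significant result leaves open.** SE = √(2/48) = 0.204 SD. The 95% half-width is 1.986 × 0.204 = 0.41 SD (0.36 SD with 60 per arm). An observed difference of exactly zero would still leave a deficit of 0.4 SD inside the interval with 48 per arm. An observed deficit just short of significance, about 0.405 SD, would have an upper bound near 0.405 + 0.405 = 0.81 SD.

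**4. What the trial could show as a non-inferiority trial.** Arms truly equal, one-sided 2.5%: power = Φ(margin/SE − 1.96). The last column multiplies the SE by √(1 − 0.5²) = 0.866, for baseline adjustment at an assumed correlation of 0.5.

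| Margin | 48 per arm | 60 per arm | 48 per arm, adjusted |
|---|---|---|---|
| 0.3 SD | 31% | 38% | 40% |
| 0.4 SD | 50% | 59% | 62% |
| 0.5 SD | 69% | 78% | 81% |

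Without adjustment, 80% power at one-sided 2.5% needs 63, 99 and 175 evaluable per arm for margins of 0.5, 0.4 and 0.3 SD. Dividing by 0.8 for drop-out gives 79, 124 and 219 randomised per arm.

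**The case against.** Five points can be made for the plan.

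- **The misreading is inferred.** Nothing in the article says that p > 0.05 will be taken as similarity, and the policy wording is permissive. That is true. But no other criterion is offered, so the trigger for the recommendation is either the p-value or judgement after the data are seen.
- **The sample size may be a non-inferiority calculation in disguise.** The one-sided route to 60 is numerically the same as a 0.5 SD margin at one-sided 5%, where 48 completers per arm give 79% power. The arithmetic stands. However, the article calls 0.5 an effect size and states neither a margin nor a one-sided test. On that reading, 20% loss would still need 63 per arm, and a 0.4 SD margin at one-sided 5% would need 98.
- **48 per arm is pessimistic.** The section on reducing loss to follow-up allows the grief scale to be completed by phone, and GEE is planned. The 60-per-arm columns show the best case; the conclusion is unchanged.
- **The trial also has a general comparative aim.** Difference tests suit that aim, and GEE would yield an interval. The interval is useful only if there is a margin to read it against.
- **Equal efficacy read literally suggests equivalence.** That reading is possible, but the decision is one-directional: may three sessions replace five? Non-inferiority fits it.

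**Conclusion.** The concern holds. The protocol states an equal-efficacy hypothesis with a national policy consequence, and gives it a significance rule and an effect size that cannot support it.

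With the expected 48 completers per arm, a true deficit of 0.3 to 0.5 SD would go undetected 69% to 32% of the time (63% to 22% with no drop-out). Even an observed difference of zero would not exclude a 0.4 SD deficit.

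These figures assume a two-sided 0.05 test, equal arms, an unadjusted comparison and no clustering by center. The non-inferiority figures also rest on assumed margins. The mismatch itself rests only on the text. That a null result would be read as similarity is an inference, but the plan provides no alternative.

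**What to change.** Amend the hypothesis, sample size and analysis sections, and update the registry entry:

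1. State the primary objective as non-inferiority of three to five sessions on the grief intensity score at 3 months.
2. Give the margin in scale points, with a reason and using the pilot SD. Fix it before unblinding and before anyone sees outcomes by coded arm, since the analysts work with coded groups.
3. Set the decision rule: similarity is claimed only if the upper bound of the two-sided 95% confidence interval for three minus five lies below the margin.
4. Add a sentence that a non-significant difference will not be interpreted as similar efficacy.
5. Repeat the analysis in those who attended their allocated sessions, because missed sessions pull the arms together.
6. Restate the sample size section as the power for that margin with 120 randomised, with and without baseline adjustment.

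The cost is wording and a registry update, with no extra participants. The price is candour: unless the justified margin is about 0.5 SD and baseline adjustment helps as assumed, power falls below 80% and the trial may have to report an inconclusive result instead of similarity.
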